#### Acute response sessions

At one of the first six and at one of the final six exercise sessions, a resting blood sample will be collected immediately prior to the usual training session, immediately post-training session, 1 hour post-training session, 4 hour post-training session and immediately prior to the start of the next training session. Saliva samples will be taken in conjunction with each blood sample. Participants will be asked to abstain from caffeine and alcohol for 24 hours prior to these two acute testing sessions, and on acute testing session 2 asked to consume a similar diet to the 24 hours prior to acute session 1. During the training session, a muscle O_2_ saturation monitor will be attached to the calf muscle (non-invasively) and will be removed following the 4hour blood sample. Following the 1 hour samples, prior to the 4 hour sample, patients will be provided with light refreshments. They will be asked to refrain from consuming alcohol and caffeine and from partaking in strenuous exercise.

#### Midtraining visit

The midtraining visit will take place between weeks 3 and 5. At this visit, the experimental tests described in the baseline visit will be repeated with the exception of the VO_2 peak_ test and the accelerometer for habitual physical activity. The survey pack as described in the baseline visit will be administered, completed and collected during this visit.

#### Immediate post-training visit

The immediate post-training visit will take place within 14 days of the final exercise session taking place. All experimental tests and the survey pack outlined in the baseline visit will be repeated. An accelerometer will be fitted as in the baseline visit and returned after 1 week.

#### Three month post-training visit

The three month post-training visit will take place approximately three months following the final exercise session. The visit will be very similar to the midtraining visit. All experimental tests and the survey pack outlined in the aforementioned visit will be repeated with the exclusion of the VO_2 peak_ test. There will be no more experimental measures after this visit.

An internally designed patient satisfaction questionnaire (PSQ) will be administered once at the end of study participation. The PSQ is designed to assess the acceptability of the study and experiences of the patients in each of the trial groups with particular focus on tolerability, practicality, enjoyment and perceived usefulness of the study measures and of the study as a whole. Participants who cease involvement in the study prior the final assessments will also be invited to complete the questionnaire. This will be optional.

### Study outcome measures

#### VO_2 peak_ test

Standard ramp protocol; increasing workload of approximately 1 W every 4 s (10–15 w/min) ensuring volitional exhaustion within 12–15 min^25^ on a stationary electronically braked cycle ergometer (Lode Excalibur Sport, Groningen, Netherlands). Participants will be encouraged to cycle at a continuous cadence (~70 rpm). The highest oxygen uptake will be measured in this study (VO_2 peak_) as true maximal VO_2 _(VO_2 max_) is less commonly achieved in deconditioned and/or clinical patients. Results of this test will be used to determine training workloads.

#### Clinical information

Clinical information will be extracted from the medical notes including: age, gender, ethnicity, primary cause of renal failure, transplant type, time since transplant, dialysis duration, comorbidities, blood/urine results, current medication and smoking habits. This information will be used to primarily account for cofounding variables and analyses of differences and similarities between intervention arm groups.

#### Anthropometric measures

Anthropometric measures of height, weight and waist and hip circumference will be attained in accordance with standard protocols.^26^

#### Body composition

Bioelectrical impedance analysis performed on an InBody analyser (InBody 370, Chicago, Illinois, USA) will be used to estimate body composition (eg, body fat percentage and fat-free mass). This is a painless, non-invasive method^27 28^ previously validated for use in patients with CKD.^29^

#### Cardiovascular condition and function

A non-invasive cardiac output monitor (Cheetah Medical, Maidenhead, UK) will be used to assess heart function using cardiac bioreactance analysis. This method is safe, quick and validated^30^ for assessing haemodynamic parameters including cardiac output (heart rate x stroke volume) and total peripheral resistance.

#### Pulse wave analysis

Pulse wave analysis will be measured non-invasively to determine arterial stiffness using applanation tonometry methods (Sphygmocor, AtCor Medical, West Ryde, New South Wales, Australia). Arterial pressure waveforms are recorded superficially at the radial artery by an experienced laboratory technician by applanating the artery with a high-fidelity hand-held tonometer at the site of maximal pulsation. Consistent and reproducible waveforms are recorded for 20 s. This is a safe procedure and a measure of this type has been performed in patients with CKD previously.^13 14^

#### Physical function

Physical function will be assessed using three tests. The sit-to-stand (STS) test will be used to ascertain functional ability and has been widely used in the CKD population.^31–33^ Participants will be asked to sit on a hard upright chair with their feet flat on the floor and knees bent at 90°. One cycle is considered complete when the participant stands up and sits down again to the starting position (without using their hands). There are two tests within the STS:STS5: The time taken for patients to stand up from a seated position and sit back down again five times.STS60: The number of STS cycles achieved in 60 s and is a surrogate measure of muscular endurance.

The 4 m walk test will be used to assess gait speed. Participants will be asked to walk 4 m at their usual pace for one practice and two timed trials. The better score (in seconds) on the timed trials will be recorded.

Isometric plantar flexion strength (gastrocnemius and soleus strength) will be assessed using a modified Wii Fit board (Nintendo, Kyoto, Japan). Participants will sit with their legs bent to 90° with their feet flat on the board. A strap will be placed around the board and over the knees. Participants will then be asked to raise their heels off the board causing a downward force to be exerted on the board.

#### Muscle oxygen saturation

Prior to the acute testing sessions a small non-invasive muscle O_2_ saturation device (BSXInsight, BSXAthletics, Texas, USA) will be placed onto the calf muscle and secured with a small bandage. The device will be removed following the 4hour sample collection. This will measure muscle O_2_ saturation using NIRS and has been used in a variety of diseases previously.^34^

#### Saliva sampling and storage

Saliva samples will be collected into sterile plastic containers. Participants will swallow to empty the mouth, then open and hold the container themselves before performing a passive dribble of saliva collected under the tongue over the next 2 min. Following centrifugation, the supernatant will be aliquoted and frozen for future analysis, primarily for secretory immunoglobulin A to investigate mucosal immunity.

#### Urine sampling and storage

A urine sample will be requested during the baseline visit. This sample will be analysed for urinary protein excretion, bacteriuria and urinary tract infection susceptibility.

#### Venous blood sampling and analysis

Venous blood will be collected using venepuncture of the antecubital vein and prepared appropriately for the following analysis:A cytometric bead array technique will be used to allow bulk analysis of a panel of proinflammatory and anti-inflammatory cytokines, including but not limited to interleukin (IL)-1, IL-2, IL-6, IL-10, tumour necrosis factor-alpha and interferon gamma.Other markers of inflammation, C-reactive protein (CRP) and oxidative stress, malondialdehyde (MDA) will be assessed by ELISA.Phenotyping of microparticles using flow cytometry.Immune cell subsets using flow cytometry.Full blood count and renal profile analysis, which includes estimated glomerular filtration rate, urea, bicarbonate, creatinine, sodium, potassium and phosphate measures.

#### Questionnaires

Participants will be asked to complete a survey pack containing the following: (1) Renal Patient Outcome Scale; a validated questionnaire that measures the presence and severity of disease related symptoms with the addition of a transplant specific question set.^35^ (2) Fatigue Scale; an internally designed Likert scale on feelings of tiredness. (3) EuroQol; a short widely used quality of life questionnaire.^36^ (4) Illness Perception Questionnaire—Revised; an 84-item questionnaire which is used to assess the principle components of illness representations.^37^ This questionnaire has been tailored for patients with chronic kidney disease and will assess their perceptions of physical activity as treatment. (5) Duke Activity Status Index; a 12-item questionnaire that uses self-reported physical work capacity to estimate peak metabolic equivalents and has been shown to be a valid measurement of functional capacity.^38^ (6) Brief Pain Inventory—Short Form; a nine-item self-administered questionnaire used to evaluate the severity of a patient’s pain and the impact of this pain on the patient’s daily functioning.^39^ (7) The Pittsburgh Sleep Quality Index; a self-report questionnaire that assesses sleep quality over a onemonth time interval^40^ (8) Epworth Sleepiness Scale (ESS); the ESS measures a person’s general level of daytime sleepiness or their average sleep propensity in daily life.^41^

#### Accelerometry

An ActiGraph wGT3X-BT accelerometer (Actigraph, Pensacola, Florida, USA) will be provided to wear on the waist which will record habitual physical activity (returned after 1 week).

### Nested qualitative study (QPACE-KD)

Six participants from each intervention arm will be invited to an audiorecorded focus group or semistructured interview to discuss their experiences of the study and the intervention in more detail and to gather suggestions for relevant and acceptable design of future randomised controlled trials. The qualitative phase will be conducted by a practised researcher uninvolved with the aforementioned study protocol to encourage freedom of expression. Both one-to-one semistructured interviews and focus groups will be used to provide different but complementary qualitative information. The interviews will ascertain individual perspectives and feelings about the intervention and outcome protocol in the light of personal and individual experiences of having completed the feasibility study. On the other hand, focus groups will elicit perceptions which are particularly useful when there is some consensus and meaning about the existence of a community or shared voice.

The QPACE-KD study is an optional addition to PACE-KD. The QPACE-KD protocol will be explained to the patient, and they will be given ample opportunity to ask questions and at least 48 hours to decide whether or not to participate. If they agree, separate QPACE-KD written informed consent will be attained before the interview or focus group takes place. During the interviews and focus groups, the facilitator will introduce the process, explaining the background and reasons for the study, how the interview will proceed and details of audio recording and note taking. Participants will be reassured about the preservation of their anonymity and confidentiality as well as given the opportunity to ask questions.

Transcripts will only include non-identifying information. Individual’s names and personal details will not be included in the completed transcripts. Similarly, any written notes taken during the interviews will not include any identifiable personal data.

### Data collection and management

Data at all time points will be collected in case report forms by the trial team. All data will be entered into a secure database and will only be accessible on password-protected computers at University Hospitals of Leicester NHS Trust (UHL), University of Leicester and Loughborough University by relevant members of the study team. No identifying information will be kept in electronic form. All source data and original participant identities will be kept in a locked office in the trial site file only at UHL.

### Sample size

As the trial has a primary outcome of feasibility the study sample size is pragmatic and a power calculation is neither relevant nor possible. Data collected on secondary outcome measures will provide data on which sample size calculations can be performed in future well-informed randomised controlled trials. We have chosen specific and relevant secondary outcome variables that may be suitable future primary outcomes.

### Data analysis

The primary outcome will assess the feasibility of study components such as recruitment, randomisation, retention, assessment procedures and the implementation of the interventions. These will be quantified by analysing factors such as but not limited to: numbers screened, numbers enrolled, proportion of eligible patients enrolled, intervention-specific retention rates, rates of adherence to protocol per intervention and proportion of training sessions and assessment sessions completed. The criteria for determining study and intervention feasibility will be as follows: Compliance: attending >70% of sessions and retention/completion:>80% of participants.

Due to the small sample size, complex statistical analysis will not be performed on the secondary outcomes; however, we will use simple analysis (eg, t-test, linear regression) to investigate statistical differences for exploratory information only.

Interview data will be analysed according to the principles of interpretive thematic analysis using a framework approach^42^ to explore themes emerging from patient journeys through and experiences of the interventions and outcome measures. The whole research team, including patient partners, will be involved in qualitative analysis to avoid individual bias.

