## Methods and analysis

### PACE-KD trial design

The PACE-KD trial is a randomised, three-arm parallel-group study to determine the feasibility and acceptability of three different supervised aerobic exercise programmes. Figure 1 presents the study flow chart. There will be three parallel groups (exercise programmes): HIIT intervention A, HIIT intervention B and MICT (detailed below). Participants will be randomised to one of the three study arms and will complete 24 supervised sessions of the intervention (approximately three sessions per week over 8 weeks). After initial baseline testing, outcome measures will be attained at midtraining, immediate post-training and 3 months post-training. Additional acute outcome measures will be taken during one exercise session in the first 6 weeks and during one exercise session in the last 6 weeks of each exercise programme (see figure 2). Feasibility will be determined by assessing recruitment, compliance and completion. Acceptability and patient experience will be determined by a patient satisfaction questionnaire (PSQ) and an optional nested qualitative study (QPACE-KD) consisting of either one to one semistructured interviews or focus groups.

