### Participants and recruitment

A total of 24 participants with an established kidney transplant will be randomised (via computerised random number generator) to either HIIT intervention A, HIIT intervention B or MICT (see table 1 for detailed inclusion and exclusion criteria). Patients will be screened by their own clinician for eligibility to enter the study. Eligible patients will be approached during their routine clinical appointments and will be provided with verbal and written study information. Additionally, eligible patients who have given prior consent to be contacted regarding research opportunities will be contacted via the post. All patients will be given the opportunity to discuss the study in more detail and the opportunity to consider their participation (at least 48 hours).

**Table 1 T1:** PACE-KD inclusion and exclusion criteria

Inclusion criteria	Exclusion criteria
Diagnosed with chronic kidney disease and are a renal transplant recipient Male or female, aged 18 years or over Received renal transplant >12 weeks prior to entering the study Is willing and able to give informed consent for participation in the study	Aged under 18 years Female participants who are pregnant, lactating or planning pregnancy during the course of the study Scheduled elective surgery or other procedures requiring general anaesthesia during the study Any other significant disease or disorder* Inability to give informed consent or comply with testing and training protocol for any reason

*That is, significant comorbidity including unstable hypertension, potentially lethal arrhythmia, myocardial infarction within 6 months, unstable angina, active liver disease, uncontrolled diabetes mellitus (HbA1c≥9%), advanced cerebral or peripheral vascular disease which, in the opinion of the patient’s own clinician, may either put the patient at risk because of participation in the study or may influence the result of the study or the patient’s ability to participate in the study.

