### Study procedures

The study outcomes, measurement methods and assessment time periods are summarised in table 2, and a detailed overview of each measurement is provided at the end of this section. Data on recruitment, numbers of sessions attended and completed in accordance with the protocol and dropout will be recorded and continuously monitored.

**Table 2 T2:** PACE-KD outcomes, measurement methods and assessment time periods

Outcome	Measurement method/tool	Time period
Feasibility	Recruitment, compliance, dropout and completion percentages	Continuous
VO_2 peak_	CPET	Baseline, post-training
Physical function	Gait speed test	Baseline, midtraining, post-training, three months post-training
	Sit to stand test	
	Plantar flexion strength (Fysiometer)	
Body composition	BIA	Baseline, midtraining, post-training, three months post-training
Heart function	NICOM	Baseline, midtraining, post-training, three months post-training
Arterial stiffness	PWV (applanation tonometry)	Baseline, midtraining, post-training, three months post-training
SpO_2_	Pulse oximetry	Baseline, midtraining, post-training, three months post-training, acute response sessions
Habitual physical activity	Accelerometry	Baseline, post-training
Muscle O_2_saturation	NIRS	Acute response session
Urinary bacteriuria	Urine sample	Baseline, midtraining, post-training
Immune function	Blood and saliva samples	Baseline, midtraining, post-training, three months post-training, acute response sessions
Markers of inflammation, oxidative stress, CVD risk	Blood samples	Baseline, midtraining, post-training, three months post-training, acute response sessions
Renal profile	Blood samples	Baseline, post-training
Clinical information	Extraction from clinical notes	Baseline, midtraining, post-training, three months post-training
Renal symptoms	POS-S	Baseline, midtraining, post-training, three months post-training
Fatigue	Fatigue scale	Baseline, midtraining, post-training, three months post-training
Quality of life	EQ-5D	Baseline, midtraining, post-training, three months post-training
Illness perception	IPQ-R	Baseline, midtraining, post-training, three months post-training
Physical activity/functional capacity	DASI	Baseline, midtraining, post-training, three months post-training
Pain	BPI	Baseline, midtraining, post-training, three months post-training
Sleep quality	PSQI	Baseline, midtraining, post-training, three months post-training

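### The secondary analysis is framed as a search for statistical differences by simple tests; with three arms of about 8, baseline-adjusted differences with intervals from the regression already named would serve the stated purpose better (minor)

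*Protocol article*

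**What the plan says.** The Data analysis section of the protocol article rules out complex methods for the secondary outcomes because the sample is small. It then says "we will use simple analysis (eg, t-test, linear regression) to investigate statistical differences for exploratory information only". Both methods are given as examples. No significance level, contrast, time point or covariate is fixed there.

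The design behind that sentence is as follows.

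- **Size:** "A total of 24 participants with an established kidney transplant will be randomised" (Participants and recruitment).
- **Arms:** "There will be three parallel groups (exercise programmes): HIIT intervention A, HIIT intervention B and MICT" (PACE-KD trial design).
- **Visits:** "After initial baseline testing, outcome measures will be attained at midtraining, immediate post-training and 3 months post-training" (same section). Not every outcome is taken each time: the midtraining visit repeats the baseline tests "with the exception of the VO_2 peak_ test and the accelerometer for habitual physical activity".
- **Outcomes:** "The study outcomes, measurement methods and assessment time periods are summarised in table 2" (Study procedures).

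The Sample size section gives the purpose: "Data collected on secondary outcome measures will provide data on which sample size calculations can be performed". It adds that some of these outcomes may suit as primary outcomes of a later trial.

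**The concern.** The stated aim of the analysis and the stated use of the data do not fit well together. Planning a later trial needs a standard deviation, a sense of how uncertain it is, and an estimated difference with its interval. Whether p falls below a threshold supplies none of these.

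The test named first is also awkward here. A t-test compares two groups, so three arms mean three tests per outcome and visit. Applied to follow-up values alone, it would leave unused the baseline value that Table 2 provides for most outcomes.

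At about 8 per arm, most real differences of moderate size would be missed. Across many outcomes, some chance differences would look notable. If such results influenced which outcome is taken forward, the choice would rest largely on noise.

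**Working it through.** The plan states no power, effect size, SD or significance level, so it has no figure to reproduce. Assumptions used here: equal allocation (8 per arm), two-sided 5%, and full follow-up unless stated.

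**1. Possible comparisons.** These are the Table 2 measures with a baseline and at least one follow-up visit. Each blood panel counts as one measure, the two sit-to-stand tests count as one, and acute-session samples are left out.

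| Measures | Number | Follow-up visits | Measure-visits |
|---|---|---|---|
| Measured at all three follow-ups | 17 | 3 | 51 |
| VO2peak, accelerometry, renal profile | 3 | 1 | 3 |
| Urine | 1 | 2 | 2 |
| Total | 21 | | 56 |

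Three arms give 3 pairs, so 56 × 3 = 168 possible pairwise comparisons. If all were tested and nothing differed, 168 × 0.05 = 8.4 would reach p<0.05 on average. Correlation between outcomes does not change that expected count.

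**2. Power of a two-arm t-test, 8 v 8** (noncentral t, 14 df, noncentrality d × √(8/2)):

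| True difference | Power |
|---|---|
| 0.5 SD | 15% |
| 0.8 SD | 32% |
| 1.0 SD | 46% |
| 1.5 SD | 80% |

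**3. Precision.** For an unadjusted follow-up t-test the 95% half-width is t(0.975, 14) × √(2/8) = 2.145 × 0.5 = 1.07 SD.

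For one regression on arm (three levels) and baseline, with all 24 participants, it is t(0.975, 20) × √[(2/8)(1 − r²)(1 + 1/18)], where t = 2.086 and r is the baseline to follow-up correlation. The documents give no r, so a range is shown. As a second comparator, a t-test on change from baseline has half-width 1.072 × √[2(1 − r)].

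| Assumed r | Follow-up t-test | Change-score t-test | Regression with baseline |
|---|---|---|---|
| 0.3 | 1.07 | 1.27 | 1.02 |
| 0.5 | 1.07 | 1.07 | 0.93 |
| 0.7 | 1.07 | 0.83 | 0.77 |
| 0.8 | 1.07 | 0.68 | 0.64 |

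The regression is the narrowest in every row. At r = 0.3 its small advantage over the follow-up t-test comes from pooling the error over three arms: a two-arm regression at that correlation again gives 1.07.

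**4. Chance findings.** In a simulation with no true difference (20,000 runs, 8 per arm), the t-test was significant in 4.9% of runs at r = 0.5 and 5.0% at r = 0.7. The adjusted interval excluded zero in 5.0% and 5.1%. Adjustment leaves the chance rate where it was.

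**5. What sample size planning can take from the data.** A completion rate above 80% of 24 means at least 20 people (0.8 × 24 = 19.2). The SD pooled over three arms then has 20 − 3 = 17 df. Its 95% interval runs from √(17/30.19) = 0.75 to √(17/7.564) = 1.50 times the estimate. Required sample size scales with the SD squared, so this spans 0.56 to 2.25 times the figure based on the point estimate. That uncertainty is worth reporting, and a p-value does not show it.

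**The case against.** The best counter-argument is that this is a condensed article, that the methods are named only by example, and that covariates and contrasts normally sit in a fuller plan. Linear regression is in the same parenthesis as the t-test, so nothing excludes a baseline term. The results are labelled exploratory, the primary outcome is feasibility, and no decision rule depends on these tests. All of that stands, and it limits the severity. It does not remove the point, because the article itself sets the aim as finding statistical differences, and a better use of a method it already names costs nothing.

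A reader might infer several stronger things that the documents do not support.

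- **That 168 tests are planned.** The article commits to no set of tests; 168 is the number that Table 2 makes possible.
- **That baseline values will be ignored.** The text does not specify follow-up-only tests. That comparator is assumed here, which is why the change-score version is shown beside it.
- **That baseline adjustment avoids chance findings.** It does not (step 4).
- **That adjustment for post-randomisation clinical values is planned.** The Clinical information section says "This information will be used to primarily account for cofounding variables and analyses of differences and similarities between intervention arm groups". Table 2 shows such data being collected at later visits, but nothing says later values will be covariates or that the whole list enters one model.
- **That test results will size the next trial.** The Sample size section refers to the data, and running t-tests does not prevent SDs from being reported.

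**Conclusion.** The point holds as a minor improvement. Searching for statistical differences with about 8 per arm has little power (15% at 0.5 SD, 32% at 0.8 SD). If every possible comparison were tested and nothing differed, about 8 chance results would be expected. Neither outcome serves the planning purpose that the article states.

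The gain in precision from the alternative depends on the baseline correlation: negligible at 0.3, useful from about 0.5, and a 40% narrower interval at 0.8 (0.64 against 1.07 SD). These figures rest on equal allocation, two-sided 5%, full follow-up and an unadjusted follow-up t-test as comparator. With 7 or 6 per arm that comparator's half-width widens to 1.16 or 1.29 SD. The conclusion about feasibility, the trial's primary purpose, is not affected.

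**What to change.** Replace the sentence on simple analysis in the Data analysis section with wording to this effect: for each continuous secondary outcome and visit, fit one linear regression of the follow-up value on arm (three levels) and the baseline value. Report the adjusted mean differences between arms with 95% confidence intervals, and the SD pooled over arms with its confidence interval. Treat all of these as descriptive, with no claims of significance. Remove the t-test.

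The cost is a change of wording. Regression is already named, the baseline values are already collected, and no participant, visit or measurement is added. What is given up is the reporting of significant differences, which a trial of this size could not support.

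The number of intervals stays as large as the number of possible tests, and about 5% of them would still exclude zero by chance. The commitment not to claim significance therefore needs to be explicit.
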